### Sample Size

The trial sample size was set at 76. This estimate was based on the primary effectiveness outcome of device-measured PA (ie, steps per day over 7 days). A meaningful difference in PA was defined as an average increase of 1000 steps/day between baseline (week 0) and postintervention (week 12), based on prior literature [69]. Setting *α*=.05 and power=0.80, and accounting for 25% attrition, a target of 76 participants between the ages of 5 and 18 years, along with one of their caregivers, from Alberta Children’s Hospital or Stollery Children’s Hospital (approximately 38 per site) was established. This sample size also provides sufficient power to explore secondary effectiveness outcomes while accounting for covariates (eg, sex, gender, and other factors) and offers the opportunity to stratify the sample to examine changes by cancer versus blood disorder diagnoses and across age ranges.

Regarding qualitative data, all participants and caregivers are invited and encouraged to complete an interview at postintervention (week 12) to capture their experiences and perspectives. This approach was chosen to gain a comprehensive understanding of participants’ and caregivers’ experiences within IMPACT. Perspectives from those involved in implementation are also being collected. In these cases, health care providers who refer participants and exercise professionals involved in intervention and trial conduct are recruited purposefully, with no predetermined sample size. Instead, the principle of theoretical saturation is applied, wherein participants are recruited until no new insights emerge or specific quality improvement cycle questions have been addressed [70].

### Procedures

Following referral (health care provider or self-referral), a member of the trial team contacts the caregiver via their preferred method (ie, email, phone call, or text message) to describe the PA intervention and trial, ascertain interest, confirm eligibility, and share the link to the participant consent or assent, and caregiver consent forms via REDCap. Once consent (or assent, as appropriate) is provided by the patient (henceforth referred to as the participant) and caregiver, the participant is scheduled for a baseline (week 0) assessment, which includes the collection of the participant’s device-measured PA through a 7-day Fitbit (Google LLC) wear period and tracking log. Caregivers also complete a questionnaire covering personal and medical information, and participants and caregivers complete a series of questionnaires via REDCap assessing participant- and caregiver-reported PA as well as the participant’s quality of life, symptoms, cognition, and resource use. Participants additionally complete a physical assessment via videoconference, measuring aerobic endurance, lower body flexibility, shoulder flexion range of motion, balance, and functional mobility. Once baseline assessments are completed, participants are matched with an exercise professional and begin the 12-week, individualized, 1:1 PA intervention. Following the PA intervention, participants and caregivers complete the same assessments as at baseline (with the exception of personal and medical information, which is collected only at baseline) and are invited to complete a postintervention interview via videoconference. At 6- (week 24) and 12-month (week 52) follow-up time points, participants complete the same assessments as at baseline (week 0) and postintervention (week 12), with the exceptions of personal and medical information, which is collected only at baseline, and the interview, which is conducted only postintervention. To enhance data completeness, notifications of assessments are sent via REDCap, and reminders are sent every 3 days for up to 2 weeks if assessments are not completed at baseline, postintervention, and follow-up time points. See Figure 1 for the CONSORT diagram.

**Figure 1 figure1:**
[figure not shown]
CONSORT flowchart.

Throughout the trial, additional data aligned with the RE-AIM framework are being collected. Specifically, *reach* (ie, referral rate, number of participants excluded and reasons for exclusion, participation rate, participant and caregiver demographics, and medical information); *effectiveness* (ie, participants’ and caregivers’ perceptions of the IMPACT intervention and trial); *adoption* (ie, sources of referral and differences in referrals across hospitals); *implementation* (ie, indices of feasibility [trial retention, adherence, percentage of missing data, and participants’ and caregivers’ perceptions of feasibility], intervention delivery time, trial delivery time, expertise, cost, fidelity of intervention delivery, and adverse events); and *maintenance* (ie, semistructured interviews with participants and caregivers to explore their desire for ongoing access to the PA intervention, and the proportion of participants who continue to engage in PA through the 2 follow-ups). All data are collected by trial staff. Finally, quality improvement cycles to review and optimize the implementation of the intervention and trial are conducted every 6 months (see the “Quality Improvement Cycles” section). Data covering participants’ and caregivers’ personal and medical information, intervention fidelity, and perspectives from health care providers and exercise professionals involved in referral and trial conduct are collected. These data are collated and reviewed during meetings with an advisory board comprising participants, caregivers, trial staff, health care providers, and community partners (see the “Participant and Caregiver Involvement” section). Further information on data collection and quality improvement cycles is provided in the relevant subsections within the “Data Collection” and “Quality Improvement Cycles” sections, respectively.

### The Intervention

The PA intervention was developed over 24 months with funding support from the Strategy for Patient-Oriented Research Evidence Alliance [71] and followed a patient-oriented approach [72]. The intervention was informed by relevant literature [28,29,31,32], existing pediatric exercise oncology resources (eg, the Pediatric Cancer Patients and Survivors Engaging in Exercise for Recovery program [73,74] and the Pediatric Oncology Exercise Manual [75]), and recently developed PA guidelines and recommendation statements for pediatric patients with cancer and pediatric cancer survivors [33]. This was integrated with perspectives gathered through semistructured interviews with 11 international experts who had successfully implemented PA with pediatric patients with cancer [69,76] and 16 local health care providers (eg, oncologists, nurses, physiotherapists, child life specialists) and staff from children’s hospitals in Alberta. Semistructured interview guides were developed with support from an implementation science expert ([name]) and were informed by the Consolidated Framework for Implementation Research and the Theoretical Domains Framework [77]. Questions explored barriers and enablers to implementing PA with pediatric patients with cancer and examined factors spanning intervention characteristics, outer setting, inner setting, characteristics of individuals, and process. Additionally, during the interviews, context-specific implementation strategies were explored. Relevant literature, resources, and perspectives were integrated, and a team of researchers, exercise professionals, and health care providers (ie, the trial team) collaboratively developed and refined the PA intervention.

The resulting 12-week PA intervention, delivered via videoconference, includes sessions offered 3 times per week for 15-45 minutes and incorporates a combination of aerobic, resistance, balance, core, and flexibility exercises. Videoconference delivery allows participants to join whether they are at home or in the hospital. The intervention is tailored for each participant based on the frequency (ie, how often each exercise is completed and the number of PA sessions per week), intensity (ie, the difficulty of exercises or PA sessions), time (ie, duration of each exercise and each PA session), and type of exercise (ie, aerobic, resistance, balance, core, and flexibility). Each aspect of the intervention is modified based on participants’ needs, preferences, medical factors, age, and abilities, including how they are feeling and managing treatment-related side effects, their treatment schedules, and other considerations (eg, school or extracurricular commitments). PA sessions are provided regardless of whether participants are in the hospital or at home. Select behavior change techniques (eg, goal setting, feedback and monitoring, social support, self-monitoring) are embedded within PA sessions and discussed in an age-appropriate manner. Behavior change topics are also selected based on participant choice and ongoing conversations throughout the PA sessions. As noted above, participant autonomy is prioritized throughout. See Multimedia Appendix 2 for an overview of the PA intervention. Of note, caregivers are required to be present for each PA session, either at home or in the same room as the participant, depending on the participant’s age, functional characteristics, and preferences (see the “Safety” section). If caregivers wish, they may participate in the PA sessions after completing the Get Active Questionnaire to ensure readiness and safety for engaging in PA, although the primary focus remains on the participant [78].

All PA sessions are delivered by a trained exercise professional who has completed a comprehensive >30-hour training program comprising both educational (eg, cancer and treatment protocols) and practical components (eg, exercise prescription, delivery, behavior change support, motivational communication skills). This training included the Thrive Health Cancer and Exercise program [79], as well as pediatric cancer and exercise [80] and adolescent- and young adult–specific modules [81]. Exercise professionals also attended trial-specific training covering topics such as oncology treatment and side effects, modifying PA based on treatment-related side effects, supporting movement, and intervention processes, delivered by the trial team. Finally, they completed a scenario-based competency training session, shadowed an existing group-based PA program in the community (ie, Pediatric Cancer Patients and Survivors Engaging in Exercise for Recovery [73,74]), and practiced delivering PA via videoconference to children aged 5-14 years without a history of cancer [82].

### Safety

To ensure safe delivery of the intervention and trial, several precautions are taken. Specifically, participants are medically cleared by one of their health care providers (eg, oncologist, nurse, physiotherapist) to confirm they can safely participate in PA sessions and physical function assessments. Participants’ personal and medical information is collected as part of baseline (week 0) participant- and caregiver-reported outcomes and reviewed by the trial team, including assessors and exercise professionals. If additional information is required, the trial team consults the participants and their caregivers, the participants’ health care team, and an exercise professional with >20 years of experience delivering PA to this cohort to provide safe exercise alternatives and modifications. PA sessions are led by trained exercise professionals (see the “The Intervention” section for their training). The exercise professionals follow a detailed protocol designed to support safe delivery of PA and enable necessary modifications. During sessions, they regularly check in with participants to ask how they are feeling and whether they wish to continue exercising, and they quickly adapt exercises based on participants’ responses. Additionally, exercise professionals have participants’ full address, phone number, and emergency contact information readily available, and follow established protocols in the event of a medical emergency. Two members of the trial team (AW, [name], or [name]) also review 10% of PA sessions for each participant—see the “Implementation (Throughout)” section—using a standardized checklist covering multiple categories, providing comments specifically on safety. During assessments of physical function, see the “Assessments of Physical Function (week 0, week 12, week 24, and week 52)” section, similar safety strategies are followed. Specifically, assessors have experience conducting videoconference-based assessments with young adults and adults living with and beyond cancer [53,83,84], and have received study-specific training and practice assessing children without a history of cancer. As noted above, caregivers are present during assessments, assessors have access to participants’ medical and personal information, and 2 assessors are present to support data collection and implement emergency protocols if required.

### Data Collection

#### Assessment Timeline and Data Collection

As described above, assessments occur at baseline (week 0), postintervention (week 12), and 6- (week 24) and 12-month (week 52) follow-ups. See Table 1 for an overview of outcome measures and time points. Following the RE-AIM framework, multiple types of information are collected.

**Table 1 table1:** Outcome measures and time points.

Reach (throughout)	Effectiveness (weeks 0, 12, 24, and 52)	Adoption (throughout)	Implementation (throughout)	Maintenance (weeks 12, 24, and 52)
Referral rate (numbers and sources) Number of participants excluded and reasons for exclusion Participation rate (number of participants consenting to participate divided by the number of eligible individuals referred) Personal and medical information (ie, sex, gender, and other factors [eg, age, cancer diagnosis, sexual orientation, race/ethnicity, cultural background, and socioeconomic status]) of participating participants and caregivers (collected through caregiver-reported outcomes at baseline only) Proportion of participants from rural versus urban locations	Device-measured PA^a^ levels Participant and caregiver questionnaires (PA, quality of life, symptoms, cognitive outcomes, and resource use) Assessments of physical function (aerobic endurance, lower body flexibility, shoulder flexion range of motion, balance, and functional mobility) Interviews with participants and caregivers to explore the benefits of the PA intervention (at week 12 only) Resource use Direct and indirect costs (costs of intervention delivery and trial management)	Sources of referral Differences in referrals across referring sites	Trial retention Adherence to the PA intervention Percentage of missing data Interviews with participants and caregivers to explore their perceptions of feasibility (at week 12 only) Intervention delivery time and cost Trial delivery time and cost Expertise of exercise professionals PA session fidelity Adverse events (safety)	PA levels at 6- and 12-month follow-ups PA referral into community programs Access/use of maintenance offerings PA referral implementation

^a^PA: physical activity.

#### Reach (Throughout)

Reach is assessed using data on referral rate (numbers and sources), number of participants excluded and reasons for exclusion, participation rate (number of participants consenting divided by the number of eligible individuals referred), personal and medical information (ie, sex, gender, and other factors such as age, cancer diagnosis, sexual orientation, race/ethnicity, cultural background, and socioeconomic status) of participating participants and caregivers, and the proportion of participants from rural versus urban locations. Where possible, information is also gathered from nonparticipating individuals via the consent-to-contact form and emails to assess reasons for trial refusal and to inform understanding of barriers to participating in the PA intervention and trial.

#### Effectiveness

##### Device-Measured Physical Activity (Week 0, Week 12, Week 24, and Week 52)

Device-measured PA (ie, step count) is assessed by having participants wear a Fitbit Charge HR activity tracker and complete a tracking log for 7 days. Participants are mailed the Fitbit and sent account information (generated by trial staff) via email. They are instructed to wear the Fitbit for 7 consecutive days, for at least 10 hours per day. Along with the Fitbit, participants complete a tracking log to record wear times (eg, when they put on or removed the Fitbit, and any PA performed throughout the day). At the end of the 7-day period, participants sync their Fitbit with their account, and caregivers scan or photograph the tracking log and send a copy to trial staff via email. Participants may wear the device between assessment periods if they wish, but these data are neither collected nor analyzed. Fitbits are returned once participants complete all assessments. The participant’s step count from the 7-day period is retrieved from their Fitbit account by the trial team and averaged for each time point. Fitbits have been shown to be a reliable and valid method for collecting device-measured PA data in pediatric populations with and without chronic conditions [85-88] and have been used successfully in pediatric participants with cancer [69,89].

##### Participant and Caregiver Questionnaires (Week 0, Week 12, Week 24, and Week 52)

*Personal and medical information* is collected at baseline (week 0) from both participants and caregivers to describe their characteristics. This includes participants’ biological sex, gender, race, ethnicity, location, age, diagnosis, and year of diagnosis, as well as caregivers’ highest level of education, employment status, and annual household income. The questionnaire was developed by the trial team.

*Self-reported PA* at weeks 0, 12, 24, and 52 is assessed using a modified version of the Godin-Shephard Leisure-Time Exercise Questionnaire (m-GLTEQ) to capture frequency and duration of aerobic, resistance, flexibility, and balance training [90]. Participants complete the m-GLTEQ for themselves, regardless of age, and caregivers complete the m-GLTEQ based on both their own PA and their child’s PA behavior. Specifically, participants and caregivers report the number of times per week they (and, in the case of caregivers, both themselves and their child) engage in mild, moderate, and strenuous PA during leisure time for a minimum of 10 minutes. At baseline, they also report PA levels before their (or their child’s) cancer diagnosis, and at all other time points, they report PA over the past month. The m-GLTEQ is scored by calculating the total amount of PA (time × intensity) for each intensity and type of activity and summing the totals. Intensity is weighted using metabolic equivalents of 3, 5, and 9 for light, moderate, and strenuous PA, respectively. Higher scores indicate greater PA behavior. Reports will include total moderate-to-vigorous PA as well as total PA. The m-GLTEQ has demonstrated high reliability and validity in pediatric populations with cancer [91,92].

*Quality of life* at weeks 0, 12, 24, and 52 is assessed by both participants and caregivers using the Pediatric Quality of Life Inventory (PedsQL) 4.0 Generic Core Scales and PedsQL 3.0 Cancer Module [93,94]. Participants aged 5-7, 8-12, and 13-18 complete the Young Child Report, Child Report, and Teen Report versions of the PedsQL 4.0 Generic Core Scales and PedsQL 3.0 Cancer Module, respectively. Caregivers also complete a proxy report evaluating their child’s quality of life using the corresponding PedsQL 4.0 Generic Core Scales and PedsQL 3.0 Cancer Module. Caregivers of participants aged 5-7, 8-12, 13-18, and 18+ complete the Caregiver Report for Young Children, Caregiver Report for Children, Caregiver Report for Teens, and Caregiver Report for Young Adults, respectively. The PedsQL 4.0 Generic Core Scale includes 23 questions across 4 domains of functioning: physical, emotional, social, and school. Items are scored on a 3-point scale for the Younger Child version (5-7 years): 0 (not at all), 2 (sometimes), and 4 (a lot), and on a 5-point scale for the Child (8-12 years) and Teen (13-18 years) versions, ranging from 0 (never) to 4 (almost always). After reverse scoring, items are linearly transformed to a 0-100 scale (0=100, 1=75, 2=50, 3=25, 4=0) and averaged to generate domain and total scores. Higher scores indicate a better quality of life. The PedsQL 3.0 Cancer Module participant and caregiver reports for young children (5-7 years) include 26 items across 8 domains: pain and hurt, nausea, procedural anxiety, treatment anxiety, worry, cognitive problems, perceived physical appearance, and communication. Items are scored on a 3-point scale: 0 (not at all), 2 (sometimes), and 4 (a lot). For participants and caregivers of children aged 8-12 and teens aged 13-18, the module includes 27 items across the same 8 domains, scored on a 5-point scale ranging from 0 (never) to 4 (almost always). For both versions, items are reverse-scored, linearly transformed to a 0-100 scale, and averaged, with higher scores indicating better quality of life and fewer problems or symptoms. Both the PedsQL 4.0 Generic Core Scale and PedsQL 3.0 Cancer Module have been previously used to evaluate quality of life among pediatric participants with cancer in PA interventions [51,94], and their scores have demonstrated high reliability and validity in this population17.

*Symptoms* at weeks 0, 12, 24, and 52 are assessed by both participants and caregivers using the Symptom Screening in Pediatrics Tool (SSPedi) and mini-SSPedi, which were developed for children receiving cancer treatment and undergoing hematopoietic stem cell transplant [95]. These tools capture symptoms that are currently bothering the participant, or that bothered them in the past day. The mini-SSPedi is used for participants aged 5-7 years [95], and the SSPedi is used for participants aged 8-18 years. The mini-SSPedi includes 15 items scored on a 3-point scale ranging from 0 (not bothered at all) to 2 (extremely bothered). The SSPedi includes 15 items scored on a 5-point scale ranging from 0 (not bothered at all) to 4 (extremely bothered). For both versions, item scores are summed, yielding a total score ranging from 0 (no symptoms) to 60 (worst possible), with higher scores indicating greater symptom impact. In both versions, participants and caregivers are also asked a final (16th) open-ended question to report any other issues that have recently bothered them (or, in the case of caregivers, their child). Additionally, caregivers of participants aged 5-18 years complete a proxy report SSPedi [95], which includes the same 15 items scored on a 5-point scale from 0 (not bothered at all) to 4 (extremely bothered). Similar to the participant versions, the caregiver proxy report SSPedi sums the 15 items to yield a total score ranging from 0 (no symptoms) to 60 (worst possible), with higher scores indicating greater symptom impact. The SSPedi has demonstrated reliability and validity for assessing symptoms among pediatric participants undergoing cancer treatment or hematopoietic stem cell transplant [95].

*Cognitive executive functioning* at weeks 0, 12, 24, and 52 is assessed by caregivers using the Behavior Rating Inventory of Executive Function, Second Edition (BRIEF-2) [96]. The parent proxy report form is used for all children and adolescents [97]. The BRIEF-2 includes 9 items covering major areas of executive function—behavior, emotion, and cognitive regulation—scored on a 3-point scale: 1 (never), 2 (sometimes), and 3 (often). Caregivers indicate how often their child has experienced each problem behavior over the past 6 months. Raw scores are calculated and summed to generate a score for each subscale. Additional scoring is applied for the inconsistency, negativity, and infrequency scales. The t scores and percentiles are also calculated for each raw scale score, and 90% CIs are computed to estimate the measurement error associated with the clinical scale, index, or t scores. Higher scores indicate greater cognitive impairment. The BRIEF-2 has been used with pediatric participants with cancer [98] and has demonstrated reliability and validity in this population 94.

*Resource use* at weeks 0, 12, 24, and 52 is assessed by caregivers using a modified version of the Pathways in Autism Spectrum Disorder, Phase III Resource Use Questionnaire for Adolescents (RUQ-A; November 30, 2016) [99]. Items have been adapted to the context of this trial and population. The modified RUQ-A assesses 7 types of resources that participants may use: (1) school; (2) mental health and psychological interventions; (3) rehabilitative services (eg, occupational therapy, physiotherapy); (4) child-focused recreational activities; (5) medications; (6) additional services; and (7) caregiver time associated with treatment and care. Caregivers are asked to indicate the frequency of use and costs associated with each resource their child accessed over the past 3 months. A final open-ended question allows caregivers to report any additional resources and associated costs not captured in the listed categories. The RUQ-A is not scored, and information on validity, interrater and test-retest reliability, and responsiveness is not summarized or statistically reported [99]. The RUQ-A is flexible, allowing questions to be adapted for the population of interest [99]. Although the RUQ-A has previously been used with caregivers of children with autism [99], to our knowledge, this is the first adaptation of the modified RUQ-A for pediatric participants with cancer.

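### The mini-SSPedi total is stated as 0-60, but 15 items scored 0-2 sum to at most 30, so raw symptom totals do not share the scale the protocol claims

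*Protocol article*

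**What the plan says.** All of this stands in the Protocol article, under Participant and Caregiver Questionnaires (Week 0, Week 12, Week 24, and Week 52).

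- **Version by age (Symptoms paragraph):** "The mini-SSPedi is used for participants aged 5-7 years [95], and the SSPedi is used for participants aged 8-18 years".
- **Item coding, younger form:** "The mini-SSPedi includes 15 items scored on a 3-point scale ranging from 0 (not bothered at all) to 2 (extremely bothered").
- **Item coding, older form:** "The SSPedi includes 15 items scored on a 5-point scale ranging from 0 (not bothered at all) to 4 (extremely bothered").
- **Total score:** "For both versions, item scores are summed, yielding a total score ranging from 0 (no symptoms) to 60 (worst possible").
- **Caregiver proxy SSPedi, used for participants of every age:** "which includes the same 15 items scored on a 5-point scale from 0 (not bothered at all) to 4 (extremely bothered"), with a summed total again given as 0 to 60.

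The Quality of life paragraph has a neighbouring wording issue in the PedsQL 4.0 Generic Core Scales: "After reverse scoring, items are linearly transformed to a 0-100 scale (0=100, 1=75, 2=50, 3=25, 4=0) and averaged to generate domain and total scores". The paragraph goes on to say that higher scores mean better quality of life.

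**The concern.** Item coding, scoring rule and stated range cannot all be right for the mini-SSPedi. Either the range or the item coding is wrong, and the text does not say which. An analyst who takes the stated range at face value would treat the two self-report forms and the proxy as interchangeable 0-60 scores.

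Three features of the design make this more than a misprint:

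- Eligibility spans 5 to 18 years, so both forms can be in use.
- The form is assigned by age and assessments run to week 52, so a child can move from one form to the other during follow-up.
- The Data Analysis section says recruitment is well below target and expects the emphasis to shift to individual children's trajectories. An artefact in one child is more visible there than in a mean over 76.

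**Working it through.** **Inputs** (all from the Symptoms paragraph):

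| Form | Used for | Items | Item range | Stated total |
|---|---|---|---|---|
| mini-SSPedi | self-report, ages 5-7 | 15 | 0-2 | 0-60 |
| SSPedi | self-report, ages 8-18 | 15 | 0-4 | 0-60 |
| Proxy SSPedi | caregiver, child aged 5-18 | 15 | 0-4 | 0-60 |

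**1. Stated maximum.** Maximum total = number of items x maximum item score.

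- SSPedi: 15 x 4 = 60. Reproduces the stated figure.
- Caregiver proxy: 15 x 4 = 60. Reproduces it.
- mini-SSPedi: 15 x 2 = 30. Does not reproduce it; the stated maximum is too high by a factor of 2.

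**2. What would give 60.** The mini-SSPedi reaches 60 if its items are coded 0/2/4 (15 x 4 = 60) or its total is doubled (2 x 30 = 60). Neither is stated. The Quality of life paragraph does print 0/2/4 coding for the 3-point PedsQL young-child form, so the authors write that coding out where they use it.

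**3. Size of the artefact.** At a fraction p of maximum burden, the raw mini-SSPedi total is 30p and the raw SSPedi or proxy total is 60p. The gap is 60p - 30p = 30p.

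- p = 0.5: 15 against 30, a gap of 15.
- p = 1: 30 against 60, a gap of 30.

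As a percentage of maximum, the two forms agree: 15/30 = 30/60 = 50%.

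**4. Where it would show.**

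- Between a 5-7-year-old and an older child with the same proportional burden: the younger child reads half as high.
- Between a 5-7-year-old and the caregiver's report on the same child: the child again reads half as high.
- Within a child whose form changes at age 8: constant half-maximum burden reads 15, then 30, an apparent worsening of 15 points.
- Within a child who stays on one form: no artefact. A sum on 0-30 gives a valid change whatever maximum is printed.

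**5. How many children could change form.** Participant ages are not reported. Purely as an illustration, take the 17 children in Results (16 completed, 1 active) and assume they are spread evenly over the 14 single-year ages 5 to 18. Then 17/14 = 1.2 would be aged 7 at baseline. Nearly all of these turn 8 by week 52, and about 1.2 x 12/52 = 0.3 do so by week 12.

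**6. PedsQL 4.0 wording.** The printed map applied to raw items takes 0, 1, 2, 3, 4 to 100, 75, 50, 25, 0. Reversing once (4 - x) and multiplying by 25 gives the same values. Reversing first and then applying the printed map gives 0, 25, 50, 75, 100, which contradicts the stated direction. Only a single reversal fits the paragraph as a whole.

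**The case against.** The strongest reply is that nothing in the article commits the authors to combining the forms. The Symptoms paragraph gives scoring only. The aggregated models in Data Analysis are described as initial plans, with alternatives to be considered. No section says that the child's total will be set against the caregiver's. How to handle a change of form could reasonably sit in a fuller document that is not shown. This stands in part. A reader might infer that the two versions will be pooled and that pooled means will understate younger children's symptoms by a factor of 2. The documents do not state such pooling, and the factor of 2 also assumes that the 3-point and 5-point responses are linearly equivalent, which they do not establish. What remains is that the article itself asserts a common range that its own item coding rules out. That is a wrong statement, not an omitted detail.

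A second reply is that few children are affected. On the even-age illustration, about one child would change form by week 52. That is fair and limits the size of the problem, but the true ages are unknown and the planned emphasis is on individual children.

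A reader might also infer from the PedsQL 4.0 sentence that items are reversed twice and that quality of life would be mis-scored. The documents do not support this. The printed map together with the stated direction fixes one reversal, and the PedsQL 3.0 Cancer Module sentence describes one reversal and prints no inverse map.

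**Conclusion.** The contradiction is certain: as coded, the mini-SSPedi total runs 0-30, not 0-60. Raw totals from ages 5-7 are therefore not on the scale of the SSPedi or the caregiver proxy. The artefact is 30p points at a fraction p of maximum burden, for example 15 points at one half, under the assumption that equal fractions of maximum mean equal burden. It affects only comparisons across forms, between a young child and the proxy, or across a change of form.

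Symptoms are one of several secondary outcomes. The primary outcome (steps per day) and the target of 76 are untouched, and no data are lost. This should be corrected before the final analysis, but it does not threaten the trial's main conclusion. The PedsQL 4.0 point is a minor clarification of wording.

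**What to change.** 1. Reconcile the mini-SSPedi item coding with its range. Either state the total as 0-30, or state the 0/2/4 coding or the doubling that yields 60. The authors must say which, because the article does not show whether the coding or the range is misprinted.
2. Say that both versions are put on a common scale (percent of maximum, or mini-SSPedi total x 2) before any pooling across ages, any child-proxy comparison, or any individual trajectory that spans a change of form. Mark the visit at which a child's form changed.
3. Check which scoring was used if symptoms were among the secondary outcomes in the interim analyses; the article does not say whether they were.
4. In the PedsQL 4.0 sentence, make clear that the map from 0=100 to 4=0 is itself the reversal.

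Holding a child on the baseline form through week 52 is not a good alternative, because it conflicts with the protocol's own assignment of forms by age, and much of the data is already collected.

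The cost is a few words, one line of scoring code and a check of existing scores; no new data are needed. The limits are that a rescaled mini-SSPedi remains coarser than the SSPedi, and that linear equivalence of the two response scales is an assumption to be stated.
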